**Fig. 2 Fig2:**
[figure not shown]
Study flow of the planned cluster randomised controlled trial (O = no training). A study cycle consists of 10 weeks of data collection: 5 weeks patients of “control” and 5 weeks in patients of “intervention” general practitioners (GPs). In total there will be five cycles resulting in 50 practices (25 intervention and 25 control practices)

As described in WP1, we calculate with an estimate of 20% of patients who report the receipt of brief PA advice during their GP visit without the GP having been trained. Another study showed that a brief single-session GP training can increase patient-reported rates of GP-delivered stop-smoking advice by 20%-points on average [52]. Training GPs to deliver PA advice might be more challenging, e.g., because PA recommendations are more complex than simple advice on smoking cessation methods. Training on PA advice is thus declared to have a clinically relevant effect if higher rates of delivered PA advice of at least 13%-points can be achieved in the intervention group (33%) as compared to the control group (20%), corresponding to an odds ratio of 1.97. Sample size calculation is based on the standard χ2-test in a four-fold-table and a multiplicative correction (= 1 + 0.05*(12–1) = 1.55, i.e., assuming an intraclass correlation coefficient of 0.05 and twelve IHD patients/practice) by the design effect to account for clustering. Including a total of 600 people with IHD in 50 practices (25 per study arm) will yield a power of at least 85% in the primary analysis of the intervention effect in a logistic regression model with a random intercept effect accounting for the nested design, while adjusting for patient and practice characteristics.

It is expected that around twelve people with IHD can be recruited within a period of five weeks, hence a total of five study cycles (with a total of 25 control practices and 25 intervention practices) will be needed to reach the target sample of 600 people with IHD. Periods of data collection in both groups will be temporally close to each other to avoid influences by fluctuations in patient flow, but cannot be conducted in parallel due to logistical reasons. The potential bias which may arise from the presence of a researcher collecting data in the practices is assumed to be equally distributed over the study arms. Patients will be masked to the purpose of the study until the end of the data collection. Due to the pragmatic nature of the study, neither GPs nor researchers can be fully masked to the allocation of study arms. To mitigate the risk of contamination, standard operation data collection procedures will be developed, and researchers will not be involved in the delivery of the training.

The control group will not receive a "placebo" intervention as this may lead to lower participation rates and pose a risk of bias (e.g., if a training on the delivery of stop-smoking advice would be offered to controls, GPs might be sensitised to provide advice on other detrimental health behaviours). However, once data collection in their patients is completed, GPs of the control group will immediately be offered the same training as the intervention group. This approach will ensure high retention rates in the control group.

GPs who have not participated in a program to promote PA within the last 5 years will be eligible. There are no other inclusion or exclusion criteria for GPs.

Patients will be enrolled in the study if they are ≥ 35 years old and if they have a clinical diagnosis of IHD according to International Classification of Diseases-10 I25.-I25.9. Due to data protection regulations, it will not be possible to learn about the presence of a clinical IHD diagnosis until the patient has provided written informed consent to participate. All consecutive patients willing to participate will therefore be screened during the study interview for a self-reported IHD diagnosis made by a physician, comparable to standards in health surveys [e.g., [2]]. Only participants screened positive for IHD will be interviewed on the study outcomes. All participants will be asked for their permission to verify their IHD screening result with the medical record obtained from the practice nurse. Only patients with a clinical diagnosis will be included in the final analyses. If the pilot study shows that there is a high level of correlation between self-reported IHD and validated IHD, strategies will be developed to include people who only report IHD in their self-report in the statistical analysis of the evaluation study (e.g., sensitivity analyses). The inability to provide informed consent (e.g., language barriers) and physical handicap impeding PA will be exclusion criteria for patients. GP practices will be recruited from the online register of the regional Association of Statutory Health Insurance Physicians NRW, and from the NRW General Practice Research Network [44].

With regard to a potential broader implementation and dissemination of the training, a qualitative process evaluation (comparable to WP5) with approximately eight to twelve GPs will accompany the cRCT to explore facilitators and barriers of GPs to the routine implementation of PA advice, including reimbursement strategies for its routine provision. In addition, semi-structured qualitative telephone interviews will be conducted in a subsample of 30 to 40 people with IHD who received PA advice from a GP of the intervention group on their motivation to become more active, and on barriers and facilitators to implement the recommendations of their GP into their daily lives, one month following the GP consultation (for methodological details see WP2 and WP5).

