**Phase III: Main evaluation study by means of a pragmatic, two-arm cluster randomised controlled trial (cRCT), including process evaluation and health economic accompaniment** (study years 4–5)			
WP 6: Main evaluation study	24 months	*Primary research question*: • What is the proportion of people with IHD who report receiving brief advice on PA during a routine consultation with their GPs of the intervention group compared to GPs of the control group? *Secondary research questions*: • What is the proportion of people with IHD whose current PA level was assessed by the GP? • What is the proportion of people with IHD who received specific recommendations or information about duration, frequency, or type of PA exercise and/or patient information sheets with information about PA? • What is the proportion of people with IHD who received an offer for a follow-up appointment with the GP to monitor or discuss PA level? • How satisfied are the people with the advice they received (if so)? *Further research questions*: • What is the short-term training effect on GPs' reported attitude, opportunity, knowledge, and practical skills in providing advice on PA? *Process evaluation*: • What are facilitators and barriers of GPs to the routine implementation of PA advice, including reimbursement strategies for its routine provision? • What are the patients' experiences with the GP advice they received (if so; including facilitators and barriers for the implementation of the advice by their GPs)? *Accompanying health economic research*: • Which preferences do people with IHD have regarding outcomes on increased PA? • Is it adequate to assess health care utilisation in IHD patients with the developed questionnaire?	• Full pragmatic, two-arm cRCT with randomisation (1:1); data collection in 50 GP practices (25 per study arm) and in a study sample of *n* = 300 people with IHD per study arm *Process evaluation*: • Semi-structured qualitative interviews with people with IHD who received PA advice from a GP of the intervention group (*n* = 30–40) • Qualitative process evaluation with GPs (*n* = 8–12) *Health economic accompaniment*: • Evaluation of the DCE in people with IHD of the control group of the cRCT (see WP4, *n* = 300) • Piloting of the health care utilisation questionnaire in patients of the control group of the cRCT (*n* = 300)

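### At the conventional two-sided 5% level, 600 patients in 50 practices give about 83% power under the article's own method and inputs, not at least 85%

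*Protocol article*

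**What the plan says.** The sample size for WP6 is set out in the protocol article under Phase III, in the paragraph that follows Fig. 2.

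- Control rate: "we calculate with an estimate of 20% of patients who report the receipt of brief PA advice during their GP visit" when the GP is untrained.
- Effect: a training effect counts as clinically relevant if "at least 13%-points can be achieved in the intervention group (33%) as compared to the control group (20" per cent), "corresponding to an odds ratio of 1.97".
- Method: "Sample size calculation is based on the standard χ2-test in a four-fold-table", multiplied by a design effect of 1.55, "assuming an intraclass correlation coefficient of 0.05 and twelve IHD patients/practice".
- Result: "Including a total of 600 people with IHD in 50 practices (25 per study arm) will yield a power of at least 85" per cent. This power is attributed to the primary analysis, a random-intercept logistic model adjusted for patient and practice characteristics.

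Table 1 repeats the size of the trial: "data collection in 50 GP practices (25 per study arm") and 300 people with IHD per arm. The eligibility text for WP6 adds: "Only patients with a clinical diagnosis will be included in the final analyses". No significance level or sidedness is stated anywhere in the article.

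**The concern.** The article gives every ingredient of the calculation except alpha, so the power can be checked directly. It is worded as a lower bound. If the stated inputs do not reach that bound at the usual level, the type II error for the primary comparison is larger than the 15% a reader would take from the text. This is the only power statement for the primary outcome of the main trial. Because it is a printed result, the question is one of correctness and not of detail left to a separate analysis plan.

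**Working it through.** **Inputs from the article (WP6 sample-size paragraph):** p0 = 0.20, p1 = 0.33, ICC = 0.05, m = 12 per practice, 25 practices and 300 patients per arm, chi-square test.

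**Assumption:** two-sided alpha of 5%, because none is stated.

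**1. Figures that reproduce.**
- Odds ratio: (0.33/0.67)/(0.20/0.80) = 1.970, as stated.
- Design effect: 1 + 0.05 × (12 − 1) = 1.55, as stated.

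**2. Effective size.** 300/1.55 = 193.5 per arm.

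**3. Power, pooled chi-square.** The mean proportion is 0.265.
- Null standard error: √(2 × 0.265 × 0.735/193.5) = 0.0449.
- Alternative standard error: √((0.16 + 0.2211)/193.5) = 0.0444.
- z = (0.13 − 1.96 × 0.0449)/0.0444 ≈ 0.948, so power = 82.8%.

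The stated 85% is therefore not reproduced.

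**4. Other versions at two-sided 5%.**

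| Version | Power |
|---|---|
| Unpooled variance | 83.4% |
| Arcsine | 83.1% |
| Exact power of the chi-square test (193 and 194 per arm) | 82.9% to 83.1% |
| Noncentral chi-square | 82.6% |
| Wald test on the log odds ratio | 82.0% |
| t reference, 48 df | 81.0% to 81.9% |
| Cluster simulation (beta-binomial, 200,000 runs), z / t | 82.9% / 81.6% |
| Continuity-corrected | 79.7% |

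None reaches 85%. The continuity-corrected figure is listed for completeness; the article names the standard test.

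**5. Size needed for 85%.**
- Pooled: 205.4 per arm before clustering; 205.4 × 1.55 = 318.4 per arm, or 637 in total. Rounding up to 206 first gives 206 × 1.55 = 319.3 per arm, or 639 in total. Both are about 6% above 600.
- Unpooled: 202.5 × 1.55 × 2 ≈ 628 in total.
- In whole practices of twelve: 26 per arm gives 84.3%, 27 per arm gives 85.6%.

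**6. What would give 85% with 600 patients.**
- ICC: 300/(1 + 11 × ICC) = 205.4 gives an ICC of about 0.042, against the stated 0.05.
- Alpha: about 0.061 two-sided.
- Variance: a reduction of 1 − 193.5/205.4 ≈ 6% from covariate adjustment.
- Sidedness: a one-sided 5% test gives 89.7%; a one-sided 2.5% test gives 82.8% again.

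**The case against.** **Alpha is not stated.** The result depends on taking two-sided 5%, and a one-sided 5% test would satisfy the claim. This stands as a condition on the finding. It does not rescue the sentence, because the article announces no one-sided test and two-sided 5% is the natural reading of a chi-square test. If one-sided 5% was meant, it has to be said.

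**The 85% is claimed for the adjusted mixed model, not the bare chi-square test.** This is true, and a variance reduction of about 6% would close the gap. But the stated sizing method has no covariate term, no gain is quantified, and adjustment in a logistic model cannot be presumed to supply it. What stands is that the type II error should not be put categorically at 17% or more.

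**Details may change after the pilot.** The article lists a possible sample-size adjustment among the pilot's purposes, says that details of WP6 may change, and reports that WP6 had not begun. That makes correction easy; it does not make the printed figure right.

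**A stronger reading is tempting: that power falls further, to 77–80%, because unconfirmed patients are dropped and practices will vary in size.** The documents do not support this. The 600 people with IHD can be read as confirmed, analysed patients, and the article does not say which count is meant. It gives no confirmation rate and no spread of practice sizes. If the 600 were counted before confirmation, assumed losses of 5, 10, 15 or 20% would give 81.7, 80.3, 78.9 or 77.2%. Those loss rates are illustrations and do not come from the article.

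**Conclusion.** The stated power is wrong under the article's own method and inputs at two-sided 5%: 82.8% by the named test (83.4% unpooled), with a type II error of about 17% where at most 15% is implied. The error is small. Power stays above 80% at the stated inputs and the design is not invalidated. The conclusion rests on one assumption, the conventional alpha, and it already grants exactly twelve analysed patients in every practice. It does not extend to a claim that the planned diagnosis check lowers power further, which remains an open question about what the 600 counts.

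**What to change.** - Restate the sentence: 600 analysed patients in 50 practices give about 83% power at a two-sided 5% level, with ICC 0.05 and twelve patients per practice. State alpha and sidedness.
- If 85% is meant to come from covariate adjustment, state the variance reduction relied on (about 6%).
- Say whether the 600, and the twelve per practice, are counted before or after the record confirms IHD. Do not write in a lower power for unconfirmed patients or unequal practice sizes unless rates are available, for example from the pilot.

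This costs wording only: the printed figure becomes slightly less favourable and no patients are added. If the sponsor prefers to keep 85%, the alternative is 27 practices per arm: 54 practices and 54 × 12 = 648 patients, which is 4 practices and 48 patients more than planned.

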## Phase II) Piloting of the intervention study and of the main evaluation study

### WP5: Pilot study

Based on preliminary work of the study team [22] and as recommended according to the MRC framework [31], a feasibility study testing the practicality of the planned evaluation study (WP6) is not considered necessary. Instead, a pilot study will be carried out to evaluate implementation outcomes, including the training of GP peer trainers, recruitment and randomisation processes, content and schedule of the training, materials, methods of data collection among patients and GPs including pre-tests of the study questionnaire and potential need for sample size adjustment. The pilot study will essentially function as a “scale model” of one study cycle of the planned pragmatic, two-arm, clustered randomised controlled trial (cRCT). For each study cycle, ten GP practices will be randomised (1:1) into either the intervention or control group. A study cycle is defined as a period of 5 weeks of face-to-face, practice-based data collection in people with IHD immediately following consultation with GPs who have been trained (intervention group, *n* = 5 practices) and a period of 5 weeks of face-to-face data collection in people with IHD immediately after consultation with GPs who have not been trained (control group, n = 5 practices). Per practice, approximately twelve people with IHD will be recruited, resulting in a pilot sample of 120 people with IHD.

A process evaluation with semi-structured, problem-centred individual interviews with GPs of the pilot study and with their patients with IHD who received PA advice will also be conducted. The aim is to understand: A) to what extent training contents could be implemented into practice, which factors facilitated or hampered the transfer, and how GPs experienced the delivery of very brief PA advice, and B) patients’ experiences with received advice, and their met and unmet needs. Experiences with the study procedures will be explored in both groups. Approximately six to eight interviews per group are expected to be sufficient. Data collection will continue until reaching data saturation [42] (for methodological details see WP2). Based on the insights gained from these interviews, study processes and the training manual will be further refined.

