## Phase III) Main evaluation study by means of a pragmatic, two-arm cluster randomised controlled trial (cRCT), including process evaluation and accompanying health economic research

### WP6: Main evaluation study

Following successful implementation of WP1 to WP5, WP6 aims to evaluate the effectiveness of the developed brief, single-session, tailored GP training in increasing patient-reported proportions of GP-delivered brief advice on PA to people with IHD.

The primary outcome will be the (1) proportion of people with IHD who report having received PA advice during a routine consultation with their GP. Secondary outcomes will include the proportion of patients reporting (2a) the assessment of their PA level by the GP, (2b) the receipt of a concrete recommendation on PA (e.g., the receipt of concrete information on duration, frequency or type of PA exercise and/or patient information leaflets with information on PA), (2c) receipt of an offer for a follow-up appointment with the GP to monitor or discuss the patients’ PA level, and (2d) in the subgroup of patients with IHD who reported that they had a conversation with their GP on PA: satisfaction with the advice received. Another outcome will be (3) the short-term effect of the training on GP-reported attitude towards, opportunity and knowledge of, as well as practical skills in the delivery of PA advice, according the COM-B theory [35].

For these purposes, a pragmatic, two-armed cRCT with 1:1 randomisation will be conducted in GP practices. Since details of WP6 may change after WP5 has been completed, the design of WP6 will only be described briefly.

Primary and secondary outcomes will be collected over a five-week period of face-to-face, practice-based data collection in people with IHD immediately following their consultation with GPs who have received the developed training on PA advice (intervention group). Data collection in people with IHD immediately after their consultation with untrained GPs (control group) will also conducted in a five-week period, resulting in a total period of 10 weeks of data collection for one full study cycle (Fig. 2).

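### WP6 surveys the two arms in separate five-week blocks within each cycle, describes no variation in which arm goes first, and states no cycle or block term in the model

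*Protocol article*

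**What the plan says.** The protocol article, under WP6: Main evaluation study, gives the intervention practices a five-week collection period, and the control practices a five-week period of their own. It then gives the sum of the two: "resulting in a total period of 10 weeks of data collection for one full study cycle". The Fig. 2 caption repeats this ("A study cycle consists of 10 weeks of data collection") and gives the scale: "In total there will be five cycles resulting in 50 practices (25 intervention and 25 control practices").

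On timing, the same section offers one safeguard: "Periods of data collection in both groups will be temporally close to each other to avoid influences by fluctuations in patient flow". The limit placed on that safeguard is that collection in the two arms will not overlap; in the protocol's words, it "but cannot be conducted in parallel due to logistical reasons".

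On allocation, WP5: Pilot study describes one cycle of the planned design: "ten GP practices will be randomised (1:1) into either the intervention or control group". Neither WP5 nor WP6 describes how the order of the two blocks is chosen.

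On masking, WP6 concedes that "neither GPs nor researchers can be fully masked to the allocation of study arms". It also assumes that any bias from having a researcher in the practice is the same in both arms.

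Under Analyses WP6, the primary model is a logistic mixed model with a fixed effect for group, a random intercept for practice and five patient covariates (age, sex, education, level of PA, BMI). No term for cycle or block is listed.

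**The concern.** Randomisation balances the practices between arms. It does not balance the calendar time or the stage of fieldwork at which each arm is observed. With single-arm blocks, whatever differs between the first and second five weeks of a cycle differs between the arms too.

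The primary outcome is elicited face to face, so interviewer learning, fatigue or drift is an obvious candidate. It follows the order of work, not the distance in time. The one stated safeguard, keeping the blocks close together, is directed at patient flow and does not address it.

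If the order never changes, first/second block and arm are the same variable. No term added later could separate them, so the order has to be settled before data collection. WP6 had not started when the protocol was submitted.

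**Working it through.** **1. Do the blocks overlap?** Five weeks for control plus five weeks for intervention equals the stated ten weeks per cycle, and parallel collection is ruled out. They do not overlap, so arm and block coincide completely within each cycle.

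**2. Is the order stated?** The Fig. 2 caption names control first. The definition of a cycle in WP5 and the description in WP6 name intervention first. Order of mention therefore settles nothing, and no sentence says the order is constant, alternated or randomised.

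**3. The plan's own figures.**
- Odds ratio for 33% against 20%: (0.33/0.67)/(0.20/0.80) = 1.97, as stated.
- Design effect: 1 + 0.05 × 11 = 1.55, as stated. Effective size per arm: 300/1.55 = 193.5.
- Power by the pooled chi-square test, two-sided 5% (the significance level is not stated, so this is assumed): 82.8%, against the stated 85% or more. One-sided 5% gives 89.7%. This is a separate matter, and the present point does not depend on it.

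**4. How much of a block shift reaches the arm contrast?** Let s be a systematic second-minus-first shift in reported advice, equal in all five cycles.
- Same order in all five cycles: 5/5 of s, that is 100%.
- Order split 3:2: (3 − 2)/5 = one fifth of s. Five cycles cannot be split evenly.

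**5. Illustrative size.** The documents give no value for s, so 3 and 5 points are assumptions. With no true training effect and a 20% base rate:

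SE = √(2 × 0.20 × 0.80 / 193.5) = 0.0407

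Type I error = P(|Z + bias/SE| > 1.96)

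| Assumed shift | Order | Bias | Type I error |
|---|---|---|---|
| none | any | 0 | 5% |
| 3 points | fixed | 3 points (3/13 = 23% of the target difference) | 11.4% |
| 3 points | 3:2 | 0.6 points | 5.2% |
| 5 points | fixed | 5 points | 23.3% |

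Allowing the variance to change with the shifted rate gives 11.1%, 5.3% and 21.8% for the last three rows. In the other direction, a 3-point shift against the intervention under a fixed order lowers power from 82.8% to 62.3%.

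**6. What varying the order does not cure.** A simulation at practice level used random cycle-by-block effects with no systematic shift, left out of the analysis. With a logit SD of 0.1, 0.2, 0.3 or 0.4, the type I error was about 5.7%, 7.2%, 9.9% or 13.6%. These SDs are also assumptions. This component is the same whichever arm goes first.

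**7. Price of a block term under a 3:2 order.** Code arm and block as ±1. They agree in 30 practices and disagree in 20, so their correlation is (30 − 20)/50 = 0.2. The variance of the arm effect rises by about 1/(1 − 0.2²) = 1.04 (a linear approximation), or about 2% on the standard error. Cycle is balanced against both.

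**The case against.** The strongest reply is that the protocol never says the order is fixed. The Fig. 2 graphic, which may show the order, was not in the text examined. WP6 is expressly described only in brief, and a detailed study and analysis protocol is promised. A reader might infer from the caption that control always comes first and the whole trial is confounded with time. The text does not support that: it is silent on order, and two other places name intervention first. Confounding within each cycle is established, but confounding over the whole trial is conditional.

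The second reply concerns size. The error rates above need a shift of the same sign and size in all five cycles, and most calendar causes would not repeat so neatly. Five ten-week cycles cover 50 weeks. If run back to back (an assumption), they start at weeks 0, 10, 7, 4 and 1 of a 13-week quarter, so holidays and quarterly visits move between blocks. Such causes mostly produce cycle-specific noise, which varying the order does not remove. This stands. Interviewer learning or drift is the cause most likely to repeat, and its size is unknown.

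Third, a reader might infer that the block discloses the arm to interviewers and that this is a new fault. Disclosure requires interviewers to know the schedule, and the protocol already admits incomplete masking. It also names safeguards: standard procedures, researchers who do not deliver the training, and patients masked to the study purpose. Masking is a secondary point. What remains is that single-arm blocks sit badly with the assumption that researcher bias is equal across arms.

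Deferral to a later document does not answer the core point. An analysis plan can add a block term, but under a constant order that term cannot be estimated alongside arm.

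**Conclusion.** The point holds in conditional form. It is established that each cycle consists of two non-overlapping single-arm blocks, that no randomisation or alternation of their order is described, and that the stated model has neither a cycle nor a block term. It is not established that the order is the same in every cycle.

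If it is the same, a systematic block shift enters the treatment contrast in full and cannot be removed afterwards. The figure of about 11% for the type I error rests on an assumed consistent 3-point shift, a fixed order, a 20% base rate and a two-sided 5% test. It shows sensitivity and does not estimate the bias in this trial. The change is worth making because it is cheap and can only be made before collection begins.

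**What to change.** State the block order for each cycle. Randomise or alternate which arm is surveyed first, so that one order is used in three cycles and the other in two. Add cycle and first/second-block fixed effects to the primary model. If Fig. 2 already varies the order, say so in the text; then only the model terms are needed.

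The 3:2 order alone leaves one fifth of a common shift. With the order varied, the block term can be estimated and removes the rest. Neither step removes random block effects specific to a cycle, and the report should acknowledge this. Varying the order also makes the assumption of equal researcher bias across arms more plausible.

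The cost is scheduling, with the same practices, staff and weeks, plus about 4% in the variance of the arm effect for the block term. In cycles with intervention first, the training session must come earlier, and control practices wait about five weeks longer for their survey and for the training they are then offered. The stated logistical constraint excludes parallel collection; it does not exclude varying the order.
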